### Participant timeline {13}

Study subjects participate in the study for the duration from admission to the ED until discharge (home or hospitalization). The participant timeline is illustrated in Fig. 1, while Table 1 provides the schedule of events.

**Fig. 1 Fig1:**
[figure not shown]
Schematic illustration of a participant's journey through the 2-group parallel randomized controlled trial's phases of enrollment, allocation and data collection at multiple points in time during the visit

**Table 1 Tab1:** Schedule of events

Timepoint	Study period						
	Screening	Baseline	Treatment	Follow-up			
	***−t***_***1***_	0	***t***_***1***_ ***(after randomization)***	***t***_***2***_ ***(after symptom assessment)***	***t***_***3***_ ***(physician ecnounter)***	***t***_***4***_ ***(after physician encounter, up to 72h)***	***t***_***5***_ ***(post-discharge)***
**Eligibility**							
**Eligibility screen**	X						
**Informed consent**	X						
**Interventions:**							
**Randomization**		X					
***Symptom assessment***			X		X		
***Usual care***					X		
**Assessments**							
**Baseline variables**		X	X				
**Demographics**	X	X		X^a^		X^a^	
***Primary outcomes***						X	
***Secondary outcomes***				X		X	
***Routine clinical data***							X

^a^If ED flow prohibits patients from completing the survey at the intended timepoint

### Sample size {14}

In the literature, a mean PSQ-5 score of 81 and a standard deviation of 14–17 can be found [13]. Assuming a clinically relevant difference of 5 points this amounts to a standardized mean difference of around 0.3.

For a fixed sample size design, the sample size required to achieve a power of 1-β = 0.80 for the two-sample *t*-test assuming equal variances at level *α* = 0.05 (two-sided) under these assumptions amounts to 2 × 176 = 352 patients needed (nQuery Advisor®, version 7.0). The drop-out rate is expected to be medium-sized (20%) due to organizational matters regarding patient flow in the ED. However, through guidance by the study personnel and small financial incentives attrition rates are tried to be kept down. Nevertheless, a potential dilution of the treatment effect due to drop-outs is considered. It is assumed that this can be compensated by additional 20 % of patients to be randomized, and therefore the total sample size required for a fixed sample size design amounts to *n* = 440 patients (220 patients per group).

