### Trial design {8}

The study is a parallel-group, multi-center superiority trial with a randomization allocation ratio of 1:1 to either using a SAA before the physician encounter or physician encounter only (standard care) among non-urgent, self-referred walk-in patients in the ED.

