### Criteria for discontinuing or modifying allocated interventions {11b}

Patients will use the SAA with an estimated mean completion time of around 8 min. If patients decide to not finish the assessment, e.g. withdrawal of consent, they will stop using the app and are considered according to the randomized group in the intention to treat analysis but excluded from per protocol analysis.

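### The 440 patients allow for 20% missing PSQ outcomes, not for the effect dilution that the sample size section says they compensate

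*Protocol article*

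**What the plan says.** All the figures are in the Sample size {14} section of the protocol article. It cites "a mean PSQ-5 score of 81 and a standard deviation of 14–17 can be found" and continues: "Assuming a clinically relevant difference of 5 points this amounts to a standardized mean difference of around 0.3". The target is set by "the sample size required to achieve a power of 1-β = 0.80 for the two-sample" t-test, and at alpha "0.05 (two-sided) under these assumptions amounts to 2 × 176 = 352 patients needed".

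On losses it gives one rate: "The drop-out rate is expected to be medium-sized (20%) due to organizational matters regarding patient flow in the ED". It then says that "a potential dilution of the treatment effect due to drop-outs is considered. It is assumed that this can be compensated by additional" 20% of those to be randomized, and arrives at 440, or 220 per group. No separate figure for dilution appears.

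Two other sections matter. The section on protocol non-adherence and missing data {20c} makes intention-to-treat (ITT) the primary efficacy population. The section on discontinuing or modifying allocated interventions {11b} says that patients who stop the app early are "considered according to the randomized group in the intention to treat analysis" and are left out only of the per-protocol analysis.

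**The concern.** Two kinds of loss are treated as one. A patient without a PSQ score reduces the number analysed. A patient in the intervention arm who does not finish the app but does give a PSQ stays in the ITT comparison and pulls the mean difference towards zero. The first loss is repaired by dividing the sample size by (1−p). The second acts on the effect itself, and since sample size varies with 1/effect², it needs division by (1−p)².

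The sentence in Sample size {14} names the second loss and applies the repair for the first. The design allows the second to occur: non-completers remain in the ITT population, and the post-encounter survey can be collected for up to 72 hours, so a non-completer can still supply a PSQ. A reader of a null ITT result would take the trial as having 80% power after allowing for dilution, and the calculation does not support that.

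**Working it through.** **Inputs.** From Sample size {14}: difference 5 points, SMD 0.3 (implied SD 5/0.3 = 16.7), cited SD 14–17, two-sided alpha 0.05, power 0.80, drop-out 20%, total 440. From Trial design {8}: 1:1 allocation. Assumed, because the plan does not say: the share of intervention patients who give a PSQ but have no app effect, and that the 5 points is the effect in patients who use the app. Power is for the two-sample t-test that the plan uses (noncentral t, noncentrality d·√(n/2) with n per arm).

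**1. Reproduce the plan.** The normal approximation, n = 2(1.960 + 0.842)²/0.3², gives 175 per arm. The t-test solution is 175.4, so 176 per arm and 352 in total, as stated. Then 352/(1 − 0.20) = 440, also as stated.

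**2. What 440 restores.** 440 × 0.80 = 352, or 176 per arm. At the undiluted SMD of 0.3 the power is 80.1%. The inflation is exactly the allowance for 20% missing outcomes.

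**3. What 20% dilution would need.** The SMD becomes 0.3 × 0.8 = 0.24, or 4.0 points. Scaling gives 352/0.8² = 550. The t-test solution is 273.5, so 274 per arm and 548 in total, with every PSQ observed.

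**4. Power with 440 randomized and a single 20% loss.** Only intervention patients have an app effect to lose, so the dilution factor is the share of analysed intervention patients who keep it.

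| How the 20% is made up | Analysed per arm | SMD | ITT power |
|---|---|---|---|
| All lack a PSQ | 176 | 0.300 | 80.1% |
| Half lack a PSQ, half give one with no app effect | 198 | 0.3 × (1 − 0.10/0.90) = 0.267 | 75.4% |
| All give a PSQ, no app effect | 220 | 0.240 | 70.9% |

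**5. Sensitivity to the SD.** For the last row, SD 14 gives SMD 0.8 × 5/14 = 0.286 and power 84.9%. SD 17 gives 0.8 × 5/17 = 0.235 and power 69.2%.

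**6. How much dilution 440 can absorb.** With all 220 per arm observed, the SMD detectable at 80% power is 0.2677. The tolerable dilution is 1 − 0.2677/0.3 = 10.8%. At 5%, 10% and 15% dilution, power is 84.7%, 80.7% and 76.1%.

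**7. Two separate losses.** If 20% of outcomes are missing and, in addition, 20% of the analysed intervention patients have no app effect, there are 176 per arm at SMD 0.24 and power is 61.2%.

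**The case against.** The best defence is that the plan quotes only one 20%, and that where the article describes patient-flow problems they concern questionnaires. The footnote to the schedule of events and the data collection section {18a} both deal with surveys not completed on time. That points to missing PSQ scores, which 352/0.80 handles correctly. The app takes about 8 minutes, patients treated without waiting are excluded, and the only example given for stopping the app is withdrawal of consent, which may well leave no PSQ at all. This stands as a limit on the size of the problem: the documents do not say that patient flow cuts the app assessment short, so a high rate of non-completion cannot be inferred. It does not rescue the sentence, which claims to compensate dilution.

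It can also be argued that the 5 points, described under Primary outcome as a difference between the randomized groups, is already the ITT effect. On that reading no further reduction applies, but then there is no dilution left to compensate and the sentence has no purpose. The text leaves the matter open, so the power figures depend on the other reading.

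Three stronger readings are tempting and are not supported:

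- **Power is 61%.** This takes the plan's single 20% twice, once as missing outcomes and again as dilution among those analysed.
- **440 leaves no room for dilution.** If every PSQ is observed, it absorbs up to about 10.8%. Nothing remains only when the full 20% is missing.
- **440 is miscalculated because 352 × 1.20 is 422.4.** The added 88 patients are 20% of the 440 randomized, so the wording is loose and the total is right for 20% missing outcomes.

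**Conclusion.** The stated sample size reproduces and is a valid allowance for 20% missing PSQ outcomes. The statement that it compensates dilution of the treatment effect is wrong as a general claim, because the inflation used is 1/(1−p) and the SMD is left at 0.3.

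For one 20% loss, power is between 80% and 71%, depending on how many drop-outs still give a PSQ. The 71% end assumes an SMD of 0.3, a 5-point effect confined to app users and no effect in the others. At the lower end of the cited SD range, power stays above 80% even so, so a shortfall is not certain. The fault lies in what the plan says about its own power, not in the test, the alpha or the number to be randomized.

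**What to change.** Reword the end of Sample size {14} along these lines:

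> The total of 440 is 352/0.80; the 88 additional patients (20% of those randomized) allow for 20% missing PSQ outcomes. No separate allowance is made for dilution of the ITT effect by intervention patients who do not complete the app. If the 20% drop-out is the only loss, ITT power at a standardized difference of 0.3 is 80% when all drop-outs lack a PSQ, about 75% when half do, and about 71% when all give a PSQ but have no app effect.

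This replaces the statement that dilution is compensated. The section should also say whether the 5 points is the effect in app users or the difference between groups as randomized, and give the power over the cited SD range for each stated share of missing outcomes and app non-completion.

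The change is to text only. Enrolment and conduct stay as they are; the cost is a stated power that looks less favourable.

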### Recruitment {15}

Study nurses will approach patients in the waiting room of each study site to ask for participation in the study. Student assistants will assist study nurses in detecting and recruiting patients from the waiting rooms. Data collection is set to a time period of 6 months and the targeted sample size of 440 patients visiting Charité’s EDs in Berlin-Mitte and Berlin-Wedding (CCM and CVK), as well as Jüdisches Krankenhaus Berlin’s emergency practice of the association of statutory health insurance physicians (KV-Bereitschaftspraxis). It is assumed that it is realistic to reach the targeted numbers of patients since the number of patients presenting in the ED within the timeframe of 6 months is significantly higher than the number of participants needed for this study. Around 40,000 patients with the respective MTS categories (3 to 5) visited the EDs in a 6-month period in recent years (unpublished data).

## Assignment of interventions: allocation

### Sequence generation {16a}

The allocation sequence will be generated by the Institute of Medical Informatics, applying a permuted block design with random blocks stratified by study center using computer-generated random numbers. The block size will be concealed until the primary endpoint will be analyzed. Throughout the study, the randomization will be conducted by the Institute of Medical Informatics. The randomization list remains with the Institute of Medical Informatics for the whole duration of the study. Thus, randomization will be conducted without any influence of the principal investigator, study personnel, or physicians.

### Concealment mechanism {16b}

In every study site, sealed opaque envelopes with printed randomization numbers will be available. For each randomization number, the study group can be found inside the envelopes.

### Implementation {16c}

The allocation sequence will be generated by the Institute of Medical Informatics. The study nurse will open the envelope and will find the treatment condition for the randomized patient. Then, the study nurse will provide patients with information about treatment allocation.

## Assignment of interventions: blinding

### Who will be blinded {17a}

Due to the nature of the intervention, neither participants nor staff can be blinded to allocation.

Data analysts will be blinded for analysis of primary outcomes. Data analysts cannot be blinded for analysis of all outcome measures as data for some secondary and other outcome measures are specific to the intervention, e.g. measures on the usability of the symptom assessment application.

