#### Secondary outcomes

The secondary outcomes are as follows:Patients’ satisfaction with the patient-physician interaction is measured using the ZUF-8 [13] (German version of the Client Satisfaction Questionnaire, CSQ-8 [14]). We expect a 1-point mean increase (scale 8–32) between the intervention group and the control group after patients have been treated (at the end of the ED visit before discharge, in exceptional cases by telephone within 72h). In contrast to the PSQ, the CSQ measures satisfaction with the provided health care services.Anxiety is measured using a visual analog scale (VAS-A) [15] at baseline, after the symptom assessment, and at the end of the ED visit. We expect that the potential increase in anxiety after symptom assessment from the baseline value will not be higher than 5 points in the intervention group and that the proportion of patients leaving the ED with higher anxiety values than at baseline will not be higher in the intervention group than in the control group.Physicians’ satisfaction with the patient-physician-interaction as measured by the mean score of the physician version of the Patient Satisfaction Questionnaire (PSQ, physician version) [12]. The intervention regarding this endpoint is considered successful if we find a mean difference in means of at least 5 points (scale 0–100) in the intervention group compared to the control group after patients have been treated.

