## Statistical methods

### Statistical methods for primary and secondary outcomes {20a}

R 4.0.2 or higher (R Core Team, 2022) and SAS 9.4 (SAS Institute, USA) will be used to perform statistical analyses. Baseline characteristics will be presented as percentages (binary data), median and interquartile range (ordinal data), and mean and standard deviation (continuous data). The primary efficacy endpoint is the mean difference in the patients’ rating of patient-physician interaction (PSQ-5) between the intervention group and the control group after patients have been treated (final value) and will be analyzed with a linear mixed model accounting for recruiting site. Secondary and exploratory efficacy endpoints will be analyzed using (generalized and mixed) linear models. Reporting will include the estimator, 95% confidence intervals, and respective *p* values. No adjustments of *p* values due to multiplicity are planned.

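### Analyst blinding is promised only for the primary outcome, though the stated reason for stopping there does not apply to four other measures collected in both arms

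*Protocol article*

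**What the plan says.** Who will be blinded {17a} first says that participants and staff cannot be blinded. It then commits as follows: "Data analysts will be blinded for analysis of primary outcomes". The limit is explained by the nature of some other data: "data for some secondary and other outcome measures are specific to the intervention, e.g. measures on the usability of the symptom assessment application".

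Secondary outcomes defines the measures that follow the primary one:

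- ZUF-8: "We expect a 1-point mean increase (scale 8–32) between the intervention group and the control group after patients have been treated".
- Anxiety (VAS-A), two expectations. The first lies within one arm: "the potential increase in anxiety after symptom assessment from the baseline value will not be higher than 5 points in the intervention group". The second compares arms: "the proportion of patients leaving the ED with higher anxiety values than at baseline will not be higher in the intervention group than in the" (the sentence ends by naming the controls).
- Physician PSQ, on a 0–100 scale against the control group: "The intervention regarding this endpoint is considered successful if we find a mean difference in means of at least 5 points".

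Other outcomes adds that the trust scale of the CPQ is measured in both groups. For the analysis, Statistical methods for primary and secondary outcomes {20a} says: "Secondary and exploratory efficacy endpoints will be analyzed using (generalized and mixed) linear models".

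**The concern.** The reason given is narrower than the limit it is used to justify. That some measures exist only in the intervention arm supports an exception for those measures. It does not support stopping the commitment at the primary outcome.

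At stake are analysis decisions on the secondary comparisons, such as covariates, the treatment of questionnaires answered late by telephone, and the handling of outliers or missing items. An analyst who knows the arms could let that knowledge shape them, even without intent. Two of these comparisons carry weight: the physician PSQ has its own success criterion, and the VAS-A comparison is where the trial would see whether the app leaves patients more anxious. Patients rate their own experience knowing their allocation, and physicians receive the app report before the consultation. Analyst masking is therefore one of the few protections still available.

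**Working it through.** No arithmetic decides this point. The check is whether the reason in {17a} fits each measure.

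| Measure | Where defined | Arms | Does the reason fit? |
|---|---|---|---|
| Patient PSQ (primary) | Primary outcome | both, compared | no; blinded analysis already promised |
| ZUF-8 | Secondary outcomes | both, compared | no |
| Physician PSQ | Secondary outcomes | both, compared | no |
| VAS-A, end of visit against baseline | Secondary outcomes | both, compared | no |
| CPQ trust scale | Other outcomes | both | no |
| VAS-A after symptom assessment | Secondary outcomes | expectation stated for the intervention group | yes |
| Self-triage certainty after the app, trust in the app | Other outcomes | intervention | yes |
| SUS, MAUQ | Other outcomes; {18a} | intervention only | yes |
| App diagnostic and triage accuracy | Other outcomes | intervention | yes |

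Three steps follow.

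1. *The VAS-A has to be split.* Explanation for the choice of comparators {6b} has controls complete questionnaires only at the start of waiting and at the end of the visit. The reading after symptom assessment would therefore reveal the arm. The baseline and final readings would not.

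2. *The example in {17a} is not a secondary outcome.* App usability is listed under Other outcomes. Among the secondary outcomes, the only element that the reason fits is the VAS-A reading after symptom assessment. All three secondary outcomes have a between-arm comparison that can be run masked.

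3. *Masking is feasible with what the trial already needs.* In {18a} the patient PSQ, ZUF-8, VAS-A and CPQ trust scale stand in one list of patient questionnaires, and only SUS and MAUQ are marked as intervention-only. A blinded primary analysis already needs coded arms and a data set without the app-only columns, because whether those columns are filled identifies the arm. The same data set can serve the other shared measures. The physician PSQ comes from a separate paper form and can be coded in the same way.

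The change does not touch the sample size calculation: 2 × 176 = 352, and 352 / 0.80 = 440, as the protocol states.

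**The case against.** The strongest reply is that {17a} contains no false statement. It says that analysts cannot be blinded for all measures because some are app-specific, and that is true. A reader might infer that the shared secondary outcomes will be analysed unblinded, but the article does not say so. It gives no commitment for them either way. This part of the reply stands and limits the point to an open gap.

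A second reply is that the detailed models, the export of data files and the release of codes belong in an analysis plan or data management plan that is not shown. That also stands in part. It is no fault of a journal article that it names only a model class, and an analysis plan fixing the models before unblinding would remove much of the risk. But the scope of analyst blinding is something this article does state, with a reason that does not support where the line is drawn.

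Third, a reader might want to put a false-positive rate on the gap. The following shows why that fails. Assume an analyst keeps the most favourable of 2, 3 or 4 models whose test statistics correlate at 0.90. The one-sided error of 2.5% then rises to 3.5%, 4.2% or 4.7% (at 0.95: 3.2%, 3.7%, 4.0%). A masked analyst who keeps the largest absolute statistic produces the same rates in favour of the app. Masking alone therefore removes none of this excess; fixing the model in advance does.

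The 2.5% frame also does not fit the outcomes. The physician PSQ criterion is an observed difference of 5 points. Assuming the patient-PSQ SD of 14–17 and 176 per arm, the standard error is SD × √(2/176), which is 1.49 to 1.81, so z = 5/SE is about 3.4 to 2.8. The anxiety expectation is that a proportion is not higher, which is not a superiority claim.

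Finally, unblinded ratings by patients and physicians are the larger source of bias. That is so, but that bias comes with the design, whereas this gap can be closed.

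**Conclusion.** The point holds as a minor, cheap improvement. The blinding commitment stops at the primary outcome, and the reason given does not cover the ZUF-8, the physician PSQ, the end-of-visit VAS-A comparison or the CPQ trust scale. The primary analysis is unaffected.

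No numerical harm is attached, because none can be supported from the document. The conclusion rests on two assumptions. The first is that the shared measures are recorded with the same variables in both arms, which the outcome definitions and the questionnaire list indicate. The second is that no unseen analysis plan already extends the masking. If one does, the article's sentence only needs to be brought into line with it.

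**What to change.** In Who will be blinded {17a}, state that analysts are blinded for every between-arm comparison: patient PSQ, ZUF-8, physician PSQ, end-of-visit VAS-A and CPQ trust. Limit the exception to intervention-only data: VAS-A after the app, certainty after the app, trust in the app, SUS, MAUQ and the app reports. Hold those data in a separate file, and release it together with the arm codes after the two-arm analyses are locked.

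The cost is one sentence, a two-step data export and a slightly later start for the intervention-only analyses. No additional patients are needed.
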